## Abstract

**Background:**

Despite considerable research on substance-abuse placement matching, evidence is still inconclusive. The aims of this exploratory trial are to evaluate (a) the effects of following matching guidelines on health-care costs and heavy drinking, and (b) factors affecting the implementation of matching guidelines in the treatment of alcohol-dependent patients.

**Methods:**

A total of 286 alcohol-dependent patients entering one of four participating detoxification units and having no arrangements for further treatment will be recruited. During the first week of treatment, all patients will be administered Measurements in the Addictions for Triage and Evaluation (MATE), European Quality of Life-Five Dimensions health status questionnaire (EQ-5D), and the Client Socio-Demographic and Service Receipt Inventory—European Version (CSSRI-EU). Patients who are randomly allocated to the intervention group will receive feedback regarding their assessment results, including clear recommendations for subsequent treatment. Patients of the control group will receive treatment as usual and, if requested, global feedback regarding their assessment results, but no recommendations for subsequent treatment. At discharge, treatment outcome and referral decisions will be recorded. Six months after discharge, patients will be administered MATE-Outcome, EQ-5D, and CSSRI-EU during a telephone interview.

**Discussion:**

This trial will provide evidence on the effects and costs of using placement-matching guidelines based on a standardized assessment with structured feedback in the treatment of alcohol-dependent patients. A process evaluation will be conducted to facilitate better understanding of the relationship between the use of guidelines, outcomes, and potential mediating variables.

**Trial registration:**

German Clinical Trials Register DRKS00005035. Registered 03 June 2013.

## Background

Patient-treatment matching in substance abuse treatment (SAT) has been the subject of extensive research. The hope has been to improve treatment outcomes by allocating each patient to the *best-fitting* treatment option. Whereas attempts to match patient characteristics with treatment modalities have so far been disappointing [1,2], there is evidence individual patients’ needs can be successfully matched with different treatment services [3,4] and treatment intensities [5-7].

In order to implement patient-treatment matching in routine care, matching guidelines have been developed and evaluated in several countries. The guidelines usually define a set of criteria that can be used to determine an appropriate treatment or level of care (LOC) for each patient. In the United States, the Patient Placement Criteria of the American Society of Addiction Medicine are the most frequently used and evaluated placement criteria [4,8,9]. Recently, in the Netherlands matching guidelines were developed, evaluated, and implemented in the context of a nationwide reorganization of the SAT [10-12]. This approach was based on existing evidence on the efficacy of placement matching; it combines the concept of stepped care with the matching of treatment services according to patients’ needs [11,12]. Depending on their history of substance abuse treatment and their degree of impairment along the dimensions of *addiction severity*, *psychiatric impairment*, and *social instability*, patients can be assigned to brief outpatient treatment (LOC1), outpatient treatment (LOC2), day/residential treatment (LOC3), or inpatient or outpatient long-term care (LOC4; [11]). *Measurements in the Addictions for Triage and Evaluation* (MATE) [13] is the assessment instrument that was developed to implement these guidelines. The MATE is feasible for use in routine care, and it provides all of the information necessary to arrive at a recommendation of one of four LOCs according to the matching guidelines [14]. Studies on the feasibility and predictive validity of the Dutch guidelines have shown promising but inconclusive results. That is, the guidelines have been implemented successfully and have been shown to be feasible to use in routine care [11], but there was no effect on drinking outcome at a nine-month follow-up assessment. The authors, therefore, recently concluded that the matching guidelines need to be revised [15]. By now, necessary revisions are still being discussed in the Netherlands. It should be recognized, however, that various complexities are involved in using matching guidelines and various factors affect how effective using them is. This includes the structure of the particular SAT service in which they are used, the number of agents involved in the decision-making process (e.g. patients, therapists, treatment centres, funding agencies), and regional variations in the availability of treatment options. It is therefore appropriate to evaluate matching guidelines according to the guidance for the development and evaluation of complex interventions [16].

The use of matching guidelines in the German SAT has also been the subject of discussion [17]. Recently, our study group conducted two pilot studies on the feasibility of using matching guidelines for patients with alcohol dependence following their participation in an inpatient withdrawal program. *Qualified withdrawal treatment* is a German-specific treatment program that includes, in addition to medically supervised detoxification, several therapeutic components aimed at enhancing patients’ motivation to remain abstinent, and referral for further treatment, if this is indicated [18]. Placement-matching decisions are often made during qualified withdrawal treatment. Our first pilot trial that included 54 alcohol-dependent patients in qualified withdrawal treatment indicated that both the setting and the procedures of the study would be feasible with minor adaptations [19]. In a second preparatory study using Delphi methodology, we asked experts in the German SAT to identify all relevant treatment options for patients with alcohol-use disorders in Germany and to organize them into four LOCs based on current evidence and discussions among the experts [20]. As a result, minor adaptations in the matching guidelines were made (see Figure 1).

**Figure 1 Fig1:**
[figure not shown]
**Adapted allocation guidelines for referral decisions after detoxifications.**

## Methods

### Trial objectives and research questions

The objectives of this study are the evaluation of the matching approach that was previously adapted to include (a) using the MATE as the standardized intake assessment, (b) a treatment recommendation for each patient based on the MATE results, and (c) a feedback session with the patient. Following the recommendations developing and evaluating complex interventions [16], we are combining evaluation of the efficacy of the intervention with a process evaluation [21]. The hypotheses regarding the effects of the matching guidelines on reduction in alcohol consumption and health service costs are as follows:

H1: Patients in the intervention group (IG) will have fewer heavy-drinking days during the 30 days prior to the follow-up interview than those in the control group (CG).

H2: Patients in the IG will have lower health-service costs during the six months after the initial assessment than those in the CG.

The process evaluation will address the following research questions:

R1: How are trial outcomes related to variations in the extent and quality of the implementation of the intervention? We expect differences between study sites due to regional variations of the participating SAT.

R2: What are the factors that mediate the effects of the intervention received on treatment outcome? Mediating variables are expected to occur at the patient level (i.e. motivation, treatment preference, sociodemographic and clinical characteristics), the treatment level (i.e. recommendations that the therapists make, overall treatment effects), and the regional level (i.e. regional variations in the availability of treatment options, whether or not funding agencies approve the treatment). Previous studies regarding placement matching imply that there may be more variables mediating the effect of the intervention than captured in the actual matching algorithm. Due to a lack of evidence for major changes to the algorithm before starting the trial, it was decided to include those variables as possible mediators.

R3: Are there subgroups that differ in their response to the intervention? We expect that patients having specific treatment needs, e.g. pregnant women or patients with severe co-morbid psychiatric or physical disorders, might differ from other patients in their response to the intervention.

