### Trial design and setting

The study is being conducted as a two-arm randomized controlled trial in four German detoxification wards offering inpatient withdrawal treatment for alcohol dependence, which lasts up to three weeks. All participating detoxification wards are located in psychiatric clinics and are specialized in withdrawal treatment for alcohol dependence. Patients with another primary or secondary psychiatric diagnosis are sometimes also referred to these wards. The assessment is being given during the first week of treatment, at treatment discharge, and six months after discharge. In the IG, an additional assessment will be given immediately after the intervention has been completed.

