### Procedure

Immediately after admission to the withdrawal unit, patients will be invited to take part in the study. A research assistant will inform patients about the study procedure, and patients who wish to participate will be asked to sign an informed consent. Patients who have done so will be asked to complete a questionnaire prior to their first assessment. This assessment will be scheduled when a patient’s withdrawal symptoms have decreased to a minimal level as judged by the medical staff. During the assessment interview, a research assistant will administer the MATE, CSSRI-EU, and EQ-5D. Finally, the research assistant will be informed by the computer-assisted MATE, whether the patient has been randomly assigned to either the IG or the CG. For patients in the IG, the research assistant will schedule the feedback session.

At the end of the withdrawal treatment, all decisions and arrangements regarding subsequent treatment will be documented for patients in both the IG and the CG. Six months after discharge from the withdrawal treatment, patients are contacted for a telephone follow-up interview, which will include the MATE-Outcomes, CSSRI-EU, and EQ-5D. Patients who complete the entire procedure including the follow-up assessment will receive payment of 30 euros. The study procedure is diagrammed in Figure 2.

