**Approximated patient flow of MATE-LOC.**

### Statistical analyses

All of the primary analyses will be conducted according to the intention-to-treat principle (ITT). There is a risk that not every patient in the IG will have a feedback session during his or her withdrawal treatment. This could result from time constraints for the therapists, unscheduled dropouts from treatment, or premature referrals for subsequent treatment. Therefore, additional per-protocol analyses will be conducted that include only those patients who actually participated in the intervention. In order to evaluate the robustness of the results, missing data will be addressed by using at least two procedures (e.g. complete case analyses, imputation by expectation-maximization, multiple imputation by chained equations), depending on the outcome and the patterns in the missing data. Differences between the two treatment arms regarding the primary outcomes will be analyzed using generalized linear models with gamma distribution and log-link function controlling for confounders (e.g. baseline costs and PDHD, age, gender, co-morbidity, EQ-5D scores). To account for correlated patient data caused by the multicenter structure, random-effect models will be applied.

Subgroup analyses will include effects of the classification as matched vs. mismatched decisions for patients in both the IG and the CG. That is, patients who received treatment according to MATE guidelines will be designated matched*,* and those who did not will be designated as mismatched. The effect of matching MATE recommendations with treatment received on the primary outcome measures will be analyzed using multiple linear regressions. Therapists’ documented reasons for deciding to deviate from MATE-LOC recommendations will also be analyzed in order to decide whether the decision algorithm should be modified. Additional exploratory analyses will be conducted to determine the relevance that patients’ demographic and clinical characteristics, their motivation for treatment, and their treatment preferences has for patient-treatment matching.

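### Research question R2 names variables fixed before randomisation as mediators; they can serve only as effect modifiers or covariates

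*Protocol article*

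**What the plan says.** R2, under Trial objectives and research questions, asks: "What are the factors that mediate the effects of the intervention received on treatment outcome". It then sorts the candidates into three levels.

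- Patient level: "Mediating variables are expected to occur at the patient level (i.e. motivation, treatment preference, sociodemographic and clinical characteristics".
- Treatment level: "recommendations that the therapists make, overall treatment effects".
- Regional level: "regional variations in the availability of treatment options, whether or not funding agencies approve the treatment".

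The paragraph closes by noting that evidence for major changes to the algorithm was lacking and that "it was decided to include those variables as possible mediators".

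Other sections settle the timing. Under Procedure, after consent, "Patients who have done so will be asked to complete a questionnaire prior to their first assessment". Process evaluation measures used during treatment says that this questionnaire covers treatment preference and the Control Preference Scale; motivation is not named there. Procedure and Randomization place disclosure of the arm after the first assessment. Under Trial design and setting, both arms are assessed in the first week, at discharge and six months later, and in addition "In the IG, an additional assessment will be given immediately after the intervention has been completed". Statistical analyses warns: "There is a risk that not every patient in the IG will have a feedback session".

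**The concern.** A mediator lies on the path from intervention to outcome: the intervention changes it, and it in turn changes the outcome. A feedback session cannot alter age, sex, severity at admission or the treatment places available in a region. Nor can it alter a preference recorded before anyone at the site knew the arm. Such variables may predict outcome, or may determine for whom and where the intervention works, but they cannot carry its effect.

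The trial is exploratory and was sized for its process evaluation, so R2 matters to what it can conclude. An analysis that followed R2 literally would look for mechanisms where none can exist. It could report chance imbalance, or selective receipt of the feedback session, as a mechanism.

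**Working it through.** **1. The roles given to the same variables.**

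| Variable | R2 | Elsewhere in the article | Can the arm change it? |
|---|---|---|---|
| Age, gender | mediator (as sociodemographic characteristics) | covariate in the primary models | no |
| Co-morbidity at baseline | mediator (as a clinical characteristic) | covariate in the primary models; if severe, an R3 subgroup | no |
| Treatment preference | mediator | only named measure precedes disclosure of the arm | not as measured |
| Motivation | mediator | timing of measurement not stated | only if measured later |
| Regional availability | mediator | source of site differences in R1 | no |
| Funding approval | mediator | non-approval recorded at follow-up (Discussion) | possible |
| Therapist recommendations | mediator | documented during treatment | possible |
| Referral concordance | not listed | called a mediator under Sample-size calculation | yes |

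Being both covariate and effect modifier is consistent. Being a mediator as well is not: adjusting the primary model for a true mediator would remove part of the effect under test.

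**2. The plan's own figure.** 100 analysable cases per arm and 30% drop-out give 100 / 0.70 = 142.9, rounded up to 143 per arm, or 286 in total. The stated size is reproduced, and nothing below changes it.

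**3. Indirect effect with the randomised arm as exposure.** The product-of-coefficients form is used for illustration; the article states no mediation model.

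Indirect effect = a × b, where a is the arm difference in the mediator and b is the slope of outcome on mediator given arm.

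For a variable fixed before randomisation, the expected value of a is 0, so the expected indirect effect is 0 whatever b is. A single estimate is not exactly zero. With 100 per arm and a mediator SD of 1:

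- SE(a) = √(2/100) = 0.141, so the variance of a is 0.02.
- With outcome residual SD 1 and 200 patients, the variance of b is about 1/200 = 0.005.
- With b = 0.3, SD(a × b) ≈ √(0.3² × 0.02 + 0.02 × 0.005) = √0.0019 = 0.044.

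For fixed regional availability, exact balance of the arms within site makes a equal to 0.

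**4. Simulation.** 5000 runs, 100 per arm. Assumed, since the documents give no such values: mediator SD 1, slope b = 0.3, direct effect 0.2, outcome residual SD 1.

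| Case | Mean indirect effect | 95% of estimates |
|---|---|---|
| (i) Baseline trait, exposure = randomised arm | 0.001 (SD 0.044) | -0.088 to 0.089 |
| (ii) Variable re-measured after randomisation, shifted 0.3 by the arm | 0.090 | 0.007 to 0.193 |
| (iii) Baseline trait, exposure = intervention received, with receipt depending on the trait | 0.080 | -0.006 to 0.182 |

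Case (i) agrees with step 3. Case (ii) is a genuine mediator: 0.3 × 0.3 = 0.09. In case (iii) the log-odds of receipt in the IG are 1.4 + 0.8 × trait, which is 1/(1 + e^-1.4) = 80% receipt at the average trait value. Patients who receive the session then differ from all others on the trait by about 0.080 / 0.3 = 0.27 SD. The trait mediates nothing, yet its mean estimate is close to that of the genuine mediator.

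**5. Precision of the interaction alternative.** With outcome SD 1 and 100 per arm, the SE of the arm difference is √(2/100) = 0.141. For a binary modifier that splits each arm in half (an assumption), the SE of the interaction is √(4/50) = 0.283, twice as large.

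**The case against.** The strongest reply is that no such analysis is planned. Statistical analyses names no mediation model. It promises exploratory work on how patient characteristics, motivation and preferences bear on matching, which fits predictor or modifier analyses equally well, and a fuller analysis plan may specify it. This stands as to the model, and the simulation is therefore an illustration. It does not remove the error: R2 states the role of these variables and says that it was decided, so a plan that implemented R2 faithfully would inherit it.

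Four stronger readings might be inferred, and the documents support none of them.

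- **That R2 returns zero by construction.** The indirect effect is zero only in expectation, and only for the randomised arm. R2 takes receipt as exposure, and there the result can be spuriously non-zero.
- **That all regional factors fail.** Funding approval is decided after randomisation and could mediate. The treatment-level items are not faulted here either.
- **That no patient-level mediator is possible.** Both arms are assessed again at discharge and at six months, the timing of motivation is not fixed, and motivation and preference can shift after feedback. Only the assessment straight after the intervention lacks a control-arm counterpart.
- **That the trial never asks who benefits, or that changes to the algorithm depend on R2.** R3 asks about differential response in subgroups and R1 about site differences. Statistical analyses bases the decision on modifying the algorithm on therapists' documented reasons for deviating from it.

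**Conclusion.** The point holds in a limited form. R2 gives the wrong analytic role to sociodemographic characteristics, baseline clinical characteristics and regional availability of treatment, and to treatment preference as far as its named measure goes. That these variables cannot mediate follows from timing and needs no numerical assumption. The figures of 0.001, 0.080 and 0.090 rest on the assumed slope, SDs and receipt model; they show direction and relative size and do not forecast this trial. The size of the spurious effect depends on how strongly a trait drives receipt, which the documents do not say.

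The consequence is confined to the process evaluation. H1, H2, their intention-to-treat analyses and the 143 per arm are untouched, and the mediator behind the sample size, referral concordance, is a proper post-randomisation variable. The correction is still worth making, because it changes what the process evaluation may claim about mechanism.

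**What to change.** 1. In R2, reclassify sociodemographic and baseline clinical characteristics, treatment preference from the pre-allocation questionnaire, and regional availability as effect modifiers, examined by arm-by-variable interaction and labelled exploratory, or as covariates.
2. Name the randomised arm as the exposure for mediation, in place of the intervention received.
3. Restrict mediation to variables that arise after randomisation and are recorded in both arms, adjusted for baseline predictors of mediator and outcome. Referral concordance at discharge qualifies, since the MATE and the final referral are documented in both arms. So does funding refusal recorded at follow-up, with a stated rule for patients who never applied.
4. Keep motivation and preference as mediators only if they are measured after randomisation in both arms. Use the IG-only assessment descriptively.
5. Leave the R3 subgroups as named. The four MATE dimension scores would not replace them, because they do not cover pregnancy or physical co-morbidity.

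The cost is rewording and reassigning variables to other models; items 1 to 3 and 5 need no new data. The drawback is low power for interactions: at 100 per arm with an even split, the standard error is twice that of the arm comparison, so a null interaction should not be read as evidence of a uniform effect.

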### Trial design and setting

The study is being conducted as a two-arm randomized controlled trial in four German detoxification wards offering inpatient withdrawal treatment for alcohol dependence, which lasts up to three weeks. All participating detoxification wards are located in psychiatric clinics and are specialized in withdrawal treatment for alcohol dependence. Patients with another primary or secondary psychiatric diagnosis are sometimes also referred to these wards. The assessment is being given during the first week of treatment, at treatment discharge, and six months after discharge. In the IG, an additional assessment will be given immediately after the intervention has been completed.

### Sample

The study will include patients with a primary diagnosis of alcohol dependence who are admitted to a qualified withdrawal program and sign an informed consent to take part in the study. Each patient’s therapist, who is a psychiatrist or a psychotherapist, will confirm the diagnosis or diagnoses at treatment entry. Exclusion criteria include being in treatment for reasons other than alcohol dependence, in crisis and needing crisis intervention, severely cognitively impaired, psychotic, illiterate, or having insufficient German language skills. Because the aim of the study is to evaluate referral decisions, an additional exclusion criterion is already having finalized plans for referral for subsequent treatment.

